The purpose of this study is to evaluate serological response and prevalence of nasopharyngeal colonization by *S. pneumoniae* in HIV+ non-hospitalized adults, following vaccination with 2 doses of PCV13.

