**Sample size and study group selection**

Applying these criteria, 50 HIV-infected adult outpatients who had never been vaccinated with any pneumococcal vaccine will be prospectively enrolled at two Infectious Diseases Clinical Centers in Central Italy (University Division of Infectious Diseases in Siena and Institute of Clinical Infectious Diseases, Catholic University of the Sacred Heart in Rome). All subjects will be required to sign a written informed consent before enrolling in the study.

At baseline (day 0, time of first vaccine dose administration), demographic, clinical and laboratory characteristics will be collected by patients interview.

At baseline, the enrolled patients will received two doses of the 13-valent vaccine (PCV13 Prevenar13®, Wyeth Vaccines) eight weeks apart.

Follow-up visits will be scheduled at 8 (time of second PCV13 dose), 24 and 48 weeks. At baseline and at each visit clinical and anamnestic data from patients will be recorded; peripheral venous blood samples will be collected to assess humoral immune response against PCV13 serotype; nasopharyngeal swabs will be collected, in order to investigate the *S. pneumonia* presence. CD4+ T cell count and plasma HIV-RNA will be also monitored.

After each vaccine administration, short- (30 minutes), medium- (≤5 days) and long-term adverse reactions will be monitored.

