**RATIONALE**

*S. pneumoniae* is frequently isolated from nasal swabs of healthy subjects, but it can also cause severe diseases (pneumonia, bacteraemia, meningitis and sepsis).HIV-infected subjects are more sensitive to invasive diseases and recurrent infection than the general population. Nasal carriage is the main pathogenetic feature for invasive disease: bacteraemia is more frequent in carriers, HIV+ patients are constantly colonized by the same pneumococcal strain and their nasopharyngeal isolates have features similar to subsequent invasive strains. A 23-valent polysaccharide vaccine (PPV23) has long been available and recommended in the HIV+ population as prophylaxis for invasive disease. Studies regarding efficacy of PPV23 in HIV+ are controversial and highlight that immune response induced by PPV23 in HIV+ is poor and an hyporesponsiveness to repeated polysaccaridic antigens stimulation can occur. Moreover, PPV23 seems not to affect pneumococcal carriage status and could lead to emergence of non-vaccine serotypes. The conjugation of pneumococcal capsular polysaccharides to carrier proteins results in an improved T-cell dependent immune response, characterized by increased antibody concentrations and induction of T and B memory cells, with a demonstrated higher efficacy in children. A heptavalent vaccine conjugated with diphtheria toxoid (PCV7) is approved in Europe since 2001 and is effective in reducing incidence of invasive disease by vaccine serotypes (4, 6B, 9V, 14, 18C, 19F, 23F), in both children and adults, due to effect of herd immunity. A PCV13 formulation has recently been developed, covering PCV7 serotypes plus 1, 3, 5, 6A, 7F and 19A. PCV13 revealed the same safety profile as PCV7 in pediatric patients, that are the main target of conjugate vaccines licensure. Some trials showed a better antibody response in terms of quantity and quality in HIV + adults by using PCV7 as compared to PPV23. However these data were not unequivocally confirmed in further studies on the use of PCV7 alone or in combination with PPV23. The first trials of PCV13 use in adults showed the same or even better response compared to PPV23, with a safety and tolerability similar to PCV7. PCV13 in HIV+ adults is a promising candidate prophylactic measure for pneumococcal infections.

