**Primary Outcome Measures:**

- Determine the rate of nasal colonization by different pneumococcal serotypes in HIV-positive and HIV-negative adults, in relation to baseline antibody titers at T0;
- Determine the basal serological response (qualitative and quantitative) in HIV-positive and HIV-negative adults;
- Define serological response after one dose of PPV23 vaccine in HIV+ adults;
- Evaluate the effect of one dose of PPV23 vaccine in terms of nasal pneumococcal carriage and occurrence of invasive pneumococcal diseases;

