**Study duration: 24 months**

**Phase I:** 12 months(November, 1st 2011 – November, 1st 2012) enrolling + microbiological and serological screening.

**Phase I:** 12 months(November, 1st 2012 – October , 31st 2013) serological and microbliological analyses and data elaboration.

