**Sample size and study group selection**

Applying these criteria, 50 HIV-infected adult outpatients and 100 subjects HIV negative will be prospectively enrolled at two Infectious Diseases Clinical Centers in Central Italy (University Division of Infectious Diseases in Siena and Institute of Clinical Infectious Diseases, Catholic University of the Sacred Heart in Rome). All subjects will be required to sign a written informed consent before enrolling in the study.

At baseline, demographic, clinical and laboratory characteristics will be collected by patients interview.

At baseline, the enrolled HIV-positive patients will received one dose of the 23-valent vaccine (PPV 23); follow-up visits will be scheduled at 8 (time of second PCV13 dose), 24 and 48 weeks.

At baseline and at each visit clinical and anamnestic data from patients will be recorded; peripheral venous blood samples will be collected to assess humoral immune response against PPV23 serotype; nasopharyngeal swabs will be collected, in order to investigate the *S. pneumonia* presence. CD4+ T cell count and plasma HIV-RNA will be also monitored.

After each vaccine administration, short- (30 minutes), medium- (≤5 days) and long-term adverse reactions will be monitored.

Oppositely, HIV negative subjects will not receive any vaccination; only at baseline clinical and anamnestic data will be recorded; peripheral venous blood samples will be collected to assess humoral immune response against PPV23 serotype; nasopharyngeal swabs will be collected, in order to investigate the *S. pneumonia* presence.

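### Change in carriage after vaccination has no named visit, no paired test and no calendar term, so season can be confounded with time since vaccination, most of all at week 24

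*Supplement*

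**What the plan says.** The sub-study (PNEUMO-HIV 2011, Primary Outcome Measures) lists "Evaluate the effect of one dose of PPV23 vaccine in terms of nasal pneumococcal carriage and occurrence of invasive pneumococcal diseases". It gives no visit, comparator or summary measure. The main study (PCV13-HIV2011) states its purpose as serological response and prevalence of colonization "in HIV+ non-hospitalized adults, following vaccination with 2 doses of PCV13". Its own primary carriage outcome relates colonization to T0 antibody titres, not to change after vaccination.

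The visit schedule is the same in both studies. Main study: "Follow-up visits will be scheduled at 8 (time of second PCV13 dose), 24 and 48 weeks". Sub-study: "follow-up visits will be scheduled at 8 (time of second PCV13 dose), 24 and 48 weeks". In the HIV-positive groups, "nasopharyngeal swabs will be collected, in order to investigate the" organism at baseline and at each visit. The sub-study's group sizes are: "50 HIV-infected adult outpatients and 100 subjects HIV negative will be prospectively enrolled". The HIV-negative subjects get no study vaccine and are assessed at baseline only.

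Enrolment is timed as "12 months(November, 1st 2011 – November, 1st 2012) enrolling + microbiological and serological screening". No monthly quota or even spread is required.

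The statistical sections of both protocols list time points for IgG but none for carriage. The paired test they name is for IgG concentrations. For proportions they name chi-squared or Fisher tests. Logistic models for colonization are planned, but covariates are not listed and neither season nor calendar time is mentioned. Under Clinical follow-up, a subject counts as colonized with at least one positive swab, with no link to a visit.

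**The concern.** A vaccine effect on carriage needs a reference that is followed over time without the study vaccine, and neither study has one. What remains is each patient's own T0 swab. A before-after comparison of this kind attributes to the vaccine anything else that changes between T0 and the follow-up visit, and season is one such thing.

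Week 24 is the exposed visit because it lies almost half a year from T0. If enrolment leans towards winter, T0 swabs lean towards winter and week-24 swabs towards spring to autumn. A seasonal fall could then be read as an effect of PPV23 or PCV13. If enrolment leans towards summer, a real fall could be hidden or turned into a rise.

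Since no visit is named, any of three follow-up visits with different seasonal exposure could become the reported one. The tests named for proportions also treat two swabs from one patient as if they came from different people.

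**Working it through.** **Inputs from the documents.** Swabs at T0 and weeks 8, 24 and 48; 50 HIV-positive patients in each study; enrolment from 1 November 2011 to 1 November 2012. The documents state no carriage rate, seasonal pattern or accrual rate, so there is no planned figure to reproduce.

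**Assumptions.** Mean carriage m = 10%; a sinusoidal season with peak:trough ratio R from 1.0 (none) to 3; peak on 15 January; no vaccine effect. The relative changes below do not depend on m.

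**Step 1, position in the year.** Degrees = 360 × days / 365.25.
- Week 8: 56 days, 55°
- Week 24: 168 days, 166°, close to the opposite season
- Week 48: 336 days, 331°, about four weeks short of the same date

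**Step 2, seasonal model.** p(t) = m[1 + a cos(2π(t − peak)/365.25)], with a = (R − 1)/(R + 1). Average p over the entry dates, then over the same dates shifted by 168 or 336 days.

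Worked case, R = 2, so a = 1/3:
- All enrolled November-April: T0 12.05%, week 24 7.87%. Change = 7.87/12.05 − 1 = −34.7%.
- All enrolled May-October: T0 7.97%, week 24 12.11%. Change = +51.9%.
- 70% in the first half-year: T0 = 0.7 × 12.05 + 0.3 × 7.97 = 10.83%; week 24 = 0.7 × 7.87 + 0.3 × 12.11 = 9.14%. Change = −15.6%.

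| R | Week 24, 70% Nov-Apr | Week 24, all Nov-Apr | Week 48, all Nov-Apr | Week 24, all May-Oct |
|---|---|---|---|---|
| 1.0 | 0% | 0% | 0% | 0% |
| 1.25 | −5.5% | −13.1% | 0.0% | +14.8% |
| 1.5 | −9.6% | −22.3% | +0.1% | +28.2% |
| 2 | −15.6% | −34.7% | +0.1% | +51.9% |
| 3 | −22.5% | −48.0% | +0.2% | +89.1% |

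With even enrolment over 12 months the average change is 0% at every visit.

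**Step 3, sensitivity.**
- Peak moved to mid-December or mid-February, all enrolled November-April, R = 1.5 to 3: week 24 −18% to −45%, week 48 −6% to +7%.
- All enrolled in November, mid-January peak, R = 1.5 to 3: week 24 −14% to −31%, week 48 −9% to −19%. Week 48 is better matched but not exact.

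**Step 4, size in patients.** At R = 2 the artefact is 50 × (0.1083 − 0.0914) = 0.8 carriers with 70% early enrolment, and 50 × (0.1205 − 0.0787) = 2.1 carriers with all early. Over R = 1.25 to 3 the ranges are 0.3 to 1.3 and 0.7 to 3.1. Against this, the 95% half-width for 12.1% versus 7.9%, treating the swabs as independent, is 1.96 × √(0.121 × 0.879/50 + 0.079 × 0.921/50) = 11.7 percentage points, for a difference of 4.2 points. Fisher's test would reach p < 0.05 in about 5% of such studies.

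**Step 5, carriage definition.** Comparing one T0 swab with any positive among three later swabs raises apparent carriage by itself: 1 − (1 − 0.10)³ = 27% against 10%, if swabs were independent. The comparison therefore needs one swab per visit.

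**The case against.** The strongest objection is that seasonality, its size, the peak date and the enrolment pattern are all assumed. That stands. A reader might infer that carriage will appear to fall by about a third. The documents do not support this: it takes roughly a 2:1 season with every patient enrolled in November-April, whereas the plan allows twelve months of enrolment. Nor is the direction fixed. The timetable gives some pressure towards early entry, since a patient enrolled on 1 November 2012 reaches week 48 on 3 October 2013, four weeks before the study ends, but that is not evidence of winter-heavy accrual.

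Second, in a self-described pilot of 50 patients the artefact is small against sampling error. This also stands: it shifts the estimate and will seldom produce significance alone.

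Third, the before-after reading is inferred. The sub-study plans a comparison with the simultaneous PCV13 cohort on the same visit weeks, which would largely cancel season if accrual were parallel. But that cohort is vaccinated too, so it compares vaccines and does not show the effect of either. The open covariate list in the logistic models would permit a calendar term but does not commit to one.

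Fourth, the Rationale describes HIV-positive patients as persistently colonized by one strain, which argues against a large within-patient swing. That is a reason to include low ratios in the range, not to ignore season.

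A reader might also take the Rationale's statement on PCV7, "in both children and adults, due to effect of herd immunity", as evidence of a falling trend in carriage. It concerns invasive disease by vaccine serotypes and gives no such support.

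**Conclusion.** The point holds in conditional form. The documents themselves establish that change in carriage has no named visit, no paired test for proportions, no calendar term and no concurrently followed group without study vaccine, and that week 24 is about half a year from T0. The bias needs two further conditions that they neither confirm nor exclude: seasonal carriage and uneven enrolment. If either is absent it is zero on average. Under the assumptions above, the week-24 artefact runs from about −5% to −23% with 70% of enrolment in November-April and from −13% to −48% with all of it then (R = 1.25 to 3), with a false rise for summer enrolment. In patients, at 10% carriage and R = 2, this is about 1 to 2 of 50.

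It is worth correcting because the sub-study outcome is primary and the correction is cheap. It does not invalidate the study. For the main study the point concerns its stated purpose, not a listed primary outcome.

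**What to change.** 1. State that change in carriage is a paired within-patient comparison, by McNemar's test or a patient-clustered logistic model, using one swab per visit and not the any-positive definition.
2. Always report T0 versus week 48, the most nearly season-matched visit, alongside weeks 8 and 24.
3. Add a sensitivity model on all swabs, clustered by patient, with a post-vaccination indicator and one sine/cosine pair for swab date. Pool both HIV-positive cohorts where possible, with a separate indicator for each vaccine.
4. Tabulate enrolment by calendar month so that readers can judge the seasonal imbalance.
5. In the sub-study, call T0 swabs pre-study-dose, not pre-vaccination. The purpose, design and inclusion criteria describe HIV-positive patients with previous PPV23, while the exclusion criteria rule it out; these sections must be reconciled.

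The cost is analysis-plan wording plus the date of each scheduled swab; no new swabs are needed. There are limits. One cohort yields at most 200 swabs, about 20 positive at 10% carriage, so the seasonal model will be imprecise even when pooled. If nearly all patients enter in one month, it can hardly separate season from time since vaccination. Week 48 has the most dropout and may miss a short-lived effect, which is why weeks 8 and 24 stay in the report.

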**Secondary Outcome Measures:**

- Pneumococcal chemosusceptibility: Number and percentages of antibiotic resistant (including multiresistant) strains
- Molecular epidemiology : Molecular typing combining PFGE (Pulsed Field Gel Electrophoresis), MLST (MultiLocus Sequence Typing) and PCR analysis of bacterial isolates

**STUDY DESIGN**

This is a prospective, multicenter, pilot controlled study enrolling HIV-infected outpatients, aged 18–65 years with CD4 counts ≥200 cells/µL, previously vaccinated , and unvaccinated HIV-negative subjects as a control,

**Study duration: 24 months**

**Phase I:** 12 months(November, 1st 2011 – November, 1st 2012) enrolling + microbiological and serological screening.

**Phase I:** 12 months(November, 1st 2012 – October , 31st 2013) serological and microbliological analyses and data elaboration.

**Inclusion Criteria:**

- > 18 years old
- obtained informed consent
- outpatient
- HIV with previous PPV23 vaccinatio (≤5years)
- HIV with CD4 ≥200 cells/µl in the last two evaluations before T0
- HIV negative regardless vaccination status

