The purpose of this study is to evaluate serological response and prevalence of nasopharyngeal colonization by *S. pneumoniae* in HIV-positive non-hospitalized adults, following vaccination with one dose of PPV23, and in unvaccinated HIV-negative subjects.

To completion of the study “Serological Response to Antipneumococcal Vaccination and Impact on *Streptococcus Pneumoniae* Nasal Carriage in HIV Adults” (protocol code PCV13-HIV2011 EudraCT number 2011-004518-40) the present study will be conducted simultaneously, for a microbiological and serological monitoring in HIV-positive adults with previous PPV23 vaccination and in HIV-negative subjects, regardless their vaccination status. Correlation analyses between clinical-anamestic data, immune response and microbiological results and the comparison between the populations from the main study (EudraCT number 2011-004518-40 ; protocol code PCV13-HIV2011) and from this sub-study (protocol code PNEUMO-HIV 2011) will provide essential clinical and epidemiologic findings useful to choice the optimal therapy and prophylaxis to prevent the pneumococcal diseases in HIV-positive adults.

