**Exclusion Criteria:**

- > 65 years old
- presence of acute infectious disease
- antibiotic therapy (ongoing or in the previous <= 7 days)
- previous PPV23 or PCV7 vaccination
- Pregnancy
- Current immunomodulatory therapy
- Immunosuppression not HIV related

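### Sub-study eligibility both requires and excludes prior PPV23; on the likelier reading its PPV23 outcomes concern a repeat dose and cannot support a PCV13-versus-PPV23 product conclusion

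*Supplement*

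**What the plan says.** The supplement holds a main-study protocol (PCV13-HIV2011) and a sub-study protocol (PNEUMO-HIV 2011). The points below are from the sub-study unless stated.

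- **Inclusion Criteria:** HIV-positive entrants must satisfy "HIV with previous PPV23 vaccinatio (≤5years". HIV-negative subjects are admitted regardless of vaccination status.
- **Exclusion Criteria:** "previous PPV23 or PCV7 vaccination", with no limit by HIV status or time since the dose. The list is the same, item for item, as the main study's.
- **Purpose statement (after the Rationale):** the study is run "for a microbiological and serological monitoring in HIV-positive adults with previous PPV23 vaccination and in HIV-negative subjects". The opening sentence of the same statement describes evaluation after vaccination with a single PPV23 dose.
- **Study Design:** the HIV-infected patients are "previously vaccinated , and unvaccinated HIV-negative subjects as a control" follows for the HIV-negative group.
- **Sample size and study group selection:** at baseline "the enrolled HIV-positive patients will received one dose of the 23-valent vaccine (PPV 23"). By contrast, "Oppositely, HIV negative subjects will not receive any vaccination".
- **Primary Outcome Measures:** one of four is "Define serological response after one dose of PPV23 vaccine in HIV+ adults". Another is the effect of one PPV23 dose on carriage and invasive disease.
- **Comparison with the main study:** the purpose statement expects it to yield "essential clinical and epidemiologic findings useful to choice the optimal therapy and prophylaxis to prevent the pneumococcal diseases in HIV-positive adults". The Statistic Analysis sections of both protocols announce further analyses using both sets of results, and name no test.
- **Main study, Sample size and study group selection:** its 50 patients have never had any pneumococcal vaccine and receive two PCV13 doses eight weeks apart.

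**The concern.** The two eligibility lists cannot both be applied to an HIV-positive patient. The protocol has two centres, and each could settle the conflict its own way, giving a cohort of mixed vaccination history.

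The conflict also decides what two primary outcomes mean. If entrants have already had PPV23 and are dosed again at baseline, the serological outcome is a revaccination response and the carriage and invasive-disease outcome is the effect of an added dose. The sub-study Rationale itself says that responsiveness can fall when polysaccharide antigens are given repeatedly.

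The comparison with the main study is affected too. If every HIV-positive sub-study patient has had PPV23 and every main-study patient is vaccine-naive, a lower response after PPV23 could come from the product or from the earlier dose. The data could not say which.

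**Working it through.** The plan gives no figure to reproduce: no effect size, SD, alpha or power stands behind its sample sizes. The main check is of the text.

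**Step 1. Apply both lists to an HIV-positive patient.**

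| Prior PPV23 history | Inclusion | Exclusion | Eligible? |
|---|---|---|---|
| Within 5 years | met | barred | no |
| More than 5 years ago | not met | barred | no |
| Never | not met | not barred | no |

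The eligible set is empty.

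**Step 2. Apply them to an HIV-negative subject.** The inclusion list admits any vaccination status, the exclusion list bars prior PPV23 or PCV7, and Study Design calls these subjects unvaccinated. A vaccinated HIV-negative subject is admitted by one section and refused by another.

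**Step 3. Which reading is better supported?** The purpose statement, Study Design and Inclusion Criteria all describe HIV-positive patients as previously vaccinated. Only the Exclusion Criteria disagree, and they match the main study's list exactly, which suggests carry-over. The group-selection section gives a baseline dose, and its contrast with HIV-negative subjects, who get none, makes sense only if the HIV-positive patients do get one.

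**Step 4. Consequence under each reading.**

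| Reading | The two PPV23 outcomes measure | Product and history separable across cohorts? |
|---|---|---|
| Prior PPV23 required, baseline dose given | a repeat dose | no: all primed in one cohort, all naive in the other |
| HIV-positive patients PPV23-naive | a first dose | this confounding disappears |
| Prior PPV23, no baseline dose | the earlier dose | no |

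Under the first reading, regression adjustment cannot help, because history does not vary within either cohort. Under every reading, the cohorts are non-randomised. From the week-8 visit onward the main study has given a second dose, while the sub-study schedules one.

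**Step 5. Illustration of size (assumed inputs).** Let h be the ratio of the post-dose geometric mean concentration (GMC) after a repeat PPV23 dose to that after a first dose, and s the SD of log10 IgG. The documents give neither. Take 50 patients per cohort (both group-selection sections), no dropout, and equal vaccines in naive patients.

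- Apparent PCV13/PPV23 ratio = 1/h: 1.11, 1.25, 1.43 and 2.0 for h = 0.9, 0.8, 0.7 and 0.5.
- SE of the difference in mean log10 IgG = s·√(2/50): 0.070, 0.090 and 0.120 for s = 0.35, 0.45 and 0.60.
- 95% margin on the ratio = 10^(1.96·SE): 1.37, 1.50 and 1.72.
- Spurious shift = −log10(h): 0.046, 0.097, 0.155 and 0.301.

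Chance, per serotype, of a significant result favouring PCV13 with no product difference (two-sided 5% t test, noncentral t, 98 df; nominal value in this direction 2.5%):

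| s | h = 0.9 | 0.8 | 0.7 | 0.5 |
|---|---|---|---|---|
| 0.35 | 10% | 28% | 59% | 99% |
| 0.45 | 7% | 19% | 40% | 91% |
| 0.60 | 6% | 12% | 25% | 70% |

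The sign can reverse. If residual antibody from the earlier dose raised the post-dose GMC to h = 1.25, the apparent ratio would be 1/1.25 = 0.80. By symmetry on the log scale, the same 19% at s = 0.45 would then favour PPV23.

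**The case against.** **The single dose may be the earlier one.** The purpose statement opens with patients studied after one PPV23 dose, so the outcome wording could refer to the dose that qualified them. The dosing paragraph also follows the main study's template and still mentions a second PCV13 dose, so it is no cleaner a source than the exclusion list. This stands far enough to keep the repeat-dose reading conditional. It does not outweigh the explicit baseline dose and the contrast with the undosed HIV-negative group.

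**No vaccine comparison is prespecified.** This stands. A reader might infer that the plan commits to a formal PCV13-versus-PPV23 test. It does not: the purpose statement speaks of comparing populations, no endpoint or test is named for that, and the paired t test given for GMCs is within-patient. The stated aim of informing the choice of prophylaxis makes a product reading likely, but not planned.

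**The population is openly described as previously vaccinated.** This also stands. A reader might infer that the plan would pass off a revaccination response as a first-dose response. The documents do not support that; the outcome label is imprecise, not concealed.

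**The carriage baseline may matter little.** The Rationale says PPV23 seems not to affect carriage, so a baseline swab after earlier PPV23 may differ little from a pre-vaccination one. No size can be put on this part.

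**The cohorts could not isolate product anyway.** They are non-randomised and differ in number of doses. This is correct. It means the caution on interpretation is needed under every resolution, including a naive HIV-positive cohort.

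**Conclusion.** The eligibility contradiction is certain and needs no assumption: as written, no HIV-positive patient qualifies for the sub-study, and the rule for HIV-negative subjects is inconsistent across three sections.

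The rest is conditional. On the better supported reading, two of the four primary outcomes concern a repeat PPV23 dose, and any response comparison with the PCV13 cohort fully confounds product with vaccination history. Non-randomised cohorts and unequal numbers of doses add to this.

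The size of any bias is unknown. The calculations show that it could range from minor (7% against a nominal 2.5% at h = 0.9, s = 0.45) to dominant (91% at h = 0.5). A reader might infer from them that the plan is biased towards PCV13, but h and s are assumed and the direction is uncertain, so they carry no weight beyond illustration. The point should be settled because it determines who is enrolled and what can be concluded.

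**What to change.** **If prior PPV23 is required and the baseline dose is given (the better supported reading):**

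- Remove prior PPV23 from the sub-study Exclusion Criteria for HIV-positive patients.
- Make Study Design, Inclusion Criteria and Exclusion Criteria agree on the vaccination status of HIV-negative subjects.
- Rename the two primary outcomes as response to, and effect of, a repeat PPV23 dose.
- State in the sub-study purpose statement and in the Statistic Analysis sections of both protocols that the cross-cohort comparison is descriptive and is not interpreted as a PCV13-versus-PPV23 product difference.

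**If HIV-positive patients are meant to be PPV23-naive:** correct the purpose statement, Study Design and Inclusion Criteria, and keep the outcome labels. The HIV-negative wording still needs reconciling, and the comparison should still be descriptive.

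**If no baseline dose is intended:** correct the group-selection section and restate the two outcomes as referring to the earlier dose. The HIV-negative wording and the descriptive status of the comparison need the same treatment. This changes the intervention and is more than an edit of wording.

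**Cost.** The first two resolutions change wording only and need no new data; under the first, the timing of the earlier PPV23 is already needed to apply the five-year limit. The downside is a narrower claim, since the two cohorts could not be presented as a comparison of vaccines.
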